## Abstract

Ultrasound hip screening is suitable for the early identification of developmental dysplasia of the hip (DDH). Newborn and infant home visits are good opportunities for hip screening in the community, but studies focusing on nurse-led screenings are lacking. Based on a pre–post design, this study aims to develop and evaluate an ultrasound training program to improve nurses’ assessment skills in detecting DDH cases during newborn and infant home visits. Said educational program will include e-learning, hands-on seminars, and clinical training. The primary outcome will be the success rate of imaging standard planes (standardized images for hip assessment) in clinical training. The secondary outcomes will include knowledge test results, objective structured clinical examination scores, time required for imaging, and inter-rater reliability between nurses and physicians. The educational program will address the issue of missed and late detection of DDH cases in resource-limited communities. This study will demonstrate the feasibility of procedures and the effectiveness of the educational program in 2024. The protocol was registered in the University Hospital Medical Information Network Clinical Trial Registry before starting the study (no. UMIN000051929, 16 August 2023).

## 1. Introduction

With more attention being paid globally to the prevention of child maltreatment, interest in the issue of hip dislocation in children is diminishing [1]. Developmental dysplasia of the hip (DDH) is associated with several risk factors, including being a woman, breech presentation, positive family history, and winter births [2,3]. According to the latest literature review published in 2023, the prevalence of DDH is approximately 1.4%, with a wide range of ethnic and cultural differences [4]. Its early detection maximizes the treatment effect by reducing medical expenditure and preventing children’s gait abnormalities [5,6]. Traditionally, physical examinations, including Ortolani and Barlow tests, are used to detect DDH cases with click sign, leg length discrepancy, and limited abduction without which experts cannot perfectly identify such cases [7]. Plain radiography is also used to detect hip dislocation, with ultrasonography being an appropriate measure for the early detection of DDH without radiation exposure [8,9,10]. Although pediatric orthopedic surgeons have developed hip screening systems in hospitals or clinics, community-based hip screening using ultrasound still needs to be further explored. 

Under the controversial debate over whether universal or selective hip screening is better [11,12], universal screening was strongly recommended in an international consensus paper [13]. In Japan, more than 90% of local governments conduct maternal and child health services [14], presenting a good opportunity for universal hip screening in communities. Newborn and infant home visits are a crucial healthcare strategy for supporting maternal and child health in each community [15]. Public health nurses and midwives have been conducting home visits for newborns and infants since the 1960s [16]. When the use of traditional Japanese-style diapers and baby clothing contributed to DDH as they extended infants’ legs, medical doctors and nurses educated caregivers on how to recommend a new diaper style that maintains the natural flex position of infants’ legs during home visits [17,18]. With the success of this health education program, the incidence of DDH in Japan has significantly decreased and now stands at approximately 0.1% [19]. However, despite home visits and infant health checkups being conducted, a nationwide survey revealed that approximately 15% of DDH cases were diagnosed after the child turned one year old [20]. The national government emphasized the necessity of finding DDH cases in each community [21]. 

The aforementioned consensus paper argues that ultrasound screening should be performed at less than six weeks of age [13], while others argue that it should not be performed before six weeks of age as the maternal estrogen-induced physiological laxity improves by the age of six weeks [22]. In Japan, screening opportunities around six weeks include one-month checkups at hospitals and clinics and newborn visits by nurses. While both opportunities for screening should be utilized, there are advantages to newborn visits in disseminating ultrasound screening. First, compared to one-month checkups, which are performed at private expense, newborn visits, which are conducted by the local government based on the legal program, would enable universal dissemination of the new technology. Second, newborn visits are generally performed between four and eight weeks, which could be a more appropriate timing for screening. Third, it is primarily pediatricians who conduct one-month checkups, not orthopedic surgeons who take initiative in ultrasound screening, making it difficult to disseminate the use of ultrasound screening. However, improving the accuracy of hip screenings in community settings is a big challenge because each local government educates nurses based on local autonomy and has limited medical resources. 

Early detection of DDH could improve the affected individuals’ quality of life and reduce their medical expenditures. Rather than manual assessments, nurses can identify suspicious DDH cases more accurately and quickly by ultrasound. Point-of-care ultrasound is an innovative and non-invasive tool for conducting physical assessment in clinical, resource-limited rural, and community settings [23,24,25]. Nurses can use it to assess abnormal cases of cardiovascular, respiratory, and gastrointestinal, and obstetrics and gynecology diseases, as well as soft tissue and joint fluid issues [23,26,27]. Using point-of-care ultrasound for the early detection of medical issues can save time, reduce radiation exposure and medical costs, and improve patients’ outcomes [28]. However, no studies have focused on conducting ultrasound hip screening by nurses in community settings [29]. Therefore, to enhance the early detection of DDH cases, this study aims to develop and evaluate an ultrasound training program to improve nurses’ assessment skills regarding DDH cases in newborns and infants during home visits. 

## 2. Materials and Methods

### 2.1. Study Design and Setting

This study is part of a research project that prevents cases of DDH from being overlooked in community settings for newborns and infants (Figure 1) [30]. Based on previous research [10,31,32] and a discussion with medical experts who supervised ultrasound hip screening at hands-on seminars conducted by the Japanese Society of Orthopedic Ultrasonics ([name], [name], [name]), we developed an educational program for nurses with a pre-post design. 

This study will be started in Okinawa Prefecture, Japan. Okinawa is a rural area with several remote islands and limited medical resources.

The protocol was registered in the University Hospital Medical Information Network Clinical Trial Registry (UMIN-CTR) before starting the study (no. UMIN000051929, 16 August 2023), which the International Committee of Medical Journal Editors approved. 

### 2.2. Participants

Participants will be recruited using snowball sampling. We will recruit approximately 30–40 nurses to consider the feasibility and limited budget. The inclusion criteria are that participants must be public health nurses, midwives, or registered nurses (any license is acceptable) who have conducted newborn and infant home visits. The exclusion criteria are individuals who are health volunteers for infant home visits and do not have a nursing license. 

Participant demographic data will be collected at study registration, including age, sex, job title, department, license, years of public health experience, years working in maternal and child health, and years of clinical experience in a hospital setting.

### 2.3. Intervention

The research team in charge of developing the educational program consisted of researchers in public health nursing and pediatric orthopedic surgeons. Before developing the materials, the first and second authors participated in a hands-on seminar on DDH assessment using ultrasound on 25–26 February 2023. The Japan Society of Orthopedic Ultrasonics organized this seminar. Researchers ([name], [name] and [name]) also participated in the nursing ultrasound hands-on seminar focusing on kidney and colon assessment on 23 July 2023. The Research Institute for Next-Generation Nursing Education (RINGNE) was in charge of providing this seminar in Japan [34]. We developed the program contents and timeline based on the skills and knowledge gained from these hands-on seminars.

The theoretical framework is Gagne’s “analysis, design, development, implementation, and evaluation model” [35]. Based on the experience gained from attending the hands-on seminar and previous research [10,31,32,33], we developed the education and training program as follows: (1) e-learning; (2) hands-on seminars; and (3) clinical training (Table 1). 

The 90 min e-learning course comprises five modules: ultrasound basics, anatomy of the hip joint, principles of the Graf method and ultrasound image reading [10], practice of the Graf method [10], and ultrasound practice and health education in the newborn home visit. The ultrasound basics module incorporates an existing module from the RINGNE, which is commonly used in nursing education in Japan [34]. The materials including anatomy of the hip joint, principles of the Graf method [10], and ultrasound image regarding its practice were developed by the co-authors ([name], [name]) [33]. They are expert orthopedic pediatricians, renowned for their extensive experience in training medical doctors in ultrasound hip screening at the Japan Society of Orthopedic Ultrasonics. Researchers ([name], [name] and [name]), with experience in public health nursing and in conducting newborn and infant home visits, developed the materials for home visits and health education. The co-authors ([name], [name] and [name]) validated all the materials and programs with the instructors’ perspectives at the Japan Society of Orthopedic Ultrasonics. Further, three nursing experts specializing in ultrasound assessment education at the RINGNE helped in developing these materials. 

Participants (nurses) will take the e-learning course after study registration, followed by an on-site hands-on seminar. The 105 min hands-on seminar comprises a lecture and practical training using phantoms. The phantom reproduces the normal hip joint. After training with the phantom, skills are evaluated by Objective Structured Clinical Examination (OSCE). Participants who pass the OSCE can proceed to the next step.

Finally, clinical training will be provided. The hip joints of infant volunteers within approximately four months, recruited by opportunity, will be examined. The first half of the clinical training will assess infants with physician supervision and guidance. In the second half of the training, participants will independently assess another infant without supervision. 

The ultrasound device *iViz air Ver.5 linear* (Fujifilm, Tokyo, Japan) will be used in all the training and examinations to standardize the procedures and readings. This device weighs 197 g, is easy to carry, and has been introduced to many home visiting nurses in Japan [31].

### 2.4. Instruments and Measures

#### 2.4.1. E-Learning

Knowledge tests on the content of each module will be incorporated for knowledge retention and evaluation. The test will evaluate the participant’s ability to distinguish normal/abnormal ultrasound images.

#### 2.4.2. Hands-On Seminar

The OSCE, which follows a practical training using a phantom, will evaluate skills in explaining ultrasound examinations, imaging, explaining assessment results to caregivers, and providing health education on DDH prevention in the newborn visit setting, by global rating (1–6) and checklist grading (0–100). 

#### 2.4.3. Clinical Training

Both medical-supervised and unsupervised examination training will be evaluated based on the success rate of imaging (0–100%), time required for imaging (seconds), and inter-rater reliability (0–1; agreement between the nurse’s assessment and the physician’s diagnosis). The assessment results from manual examination by a nurse, the results from ultrasound examination by a nurse, and the diagnostic results from a physician will be collected.

The primary outcome of this study will be the success rate in the unsupervised examination. 

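### The primary outcome scores obtaining the standard plane, and with a normal phantom and healthy infants the secondary reading measures cannot show that nurses recognise an abnormal hip

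*Protocol article*

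**What the plan says.** **Aim.** The Introduction says that "this study aims to develop and evaluate an ultrasound training program to improve nurses’ assessment skills regarding DDH cases". The Abstract frames the aim in the same way, as detection of DDH cases during home visits. The Conclusions present the programme as an answer to missed and late detection.

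**Primary outcome.** The Abstract says: "The primary outcome will be the success rate of imaging standard planes (standardized images for hip assessment) in clinical training". Section 2.4.3 narrows this to one part of the training: "The primary outcome of this study will be the success rate in the unsupervised examination". The article defines success no further, so I take it as obtaining the standard plane.

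**Reading measures.** There are three:
- In e-learning (section 2.4.1): "The test will evaluate the participant’s ability to distinguish normal/abnormal ultrasound images".
- In clinical training, both supervised and unsupervised (section 2.4.3), nurse-physician agreement: "inter-rater reliability (0–1; agreement between the nurse’s assessment and the physician’s diagnosis". Section 2.5 reports it as a PABAK for each nurse.
- Also in section 2.5, sensitivity and specificity of the nurse's manual and ultrasound examinations, with the physician's diagnosis as reference.

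**Order and material.** Section 2.3 sets the sequence: "Participants (nurses) will take the e-learning course after study registration, followed by an on-site hands-on seminar". Clinical training comes last, for those who pass the practical examination (OSCE). On the phantom, section 2.3 says: "The phantom reproduces the normal hip joint". Table 1 gives the clinical-training subjects as healthy volunteers up to four months old. Section 2.3 describes them as infant volunteers of about that age, recruited opportunistically.

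**The concern.** Ultrasound assessment has two parts: getting a valid image and judging whether the hip in it is normal. The primary outcome scores the first. A nurse who captures every plane and calls every hip normal would score 100% on it.

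That would matter little if another end-of-training outcome tested the second part on hips of both kinds. The clinical-training agreement and accuracy measures are meant to test reading, but nothing in the plan supplies abnormal hips at any scanning step. Plane success, agreement and specificity could then all look excellent in nurses who cannot recognise an abnormal hip. Missed DDH is the problem that the programme says it addresses, so the results could not support the main claim a reader will want to draw.

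**Working it through.** The article gives no sample-size calculation (30 to 40 nurses is set by feasibility and budget), so there is no figure to reproduce. The check asks what each reading measure can show.

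**Which steps present abnormal hips?**

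| Step | Reading measured? | Abnormal hips present? |
|---|---|---|
| E-learning test | Yes | Yes, as images |
| Phantom and OSCE | Technique and explanation of results | No, normal phantom |
| Supervised and unsupervised examination | Yes: agreement, sensitivity, specificity | Not planned; healthy volunteers |

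**If every infant has normal hips.** Sensitivity is true positives divided by cases, which is 0/0 and undefined. Only specificity can be estimated.

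**If some cases occur by chance.**
- Assumption: one or two distinct infants per nurse, so 30 to 80 infants. The number is not stated.
- Rates p from the Introduction: about 0.1% (Japan) and about 1.4% (literature review). I assume these apply to the volunteers.
- Expected cases = n × p. Chance of at least one = 1 − (1 − p)^n.

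| Infants | p | Expected cases | Chance of at least one |
|---|---|---|---|
| 30 | 0.1% | 0.03 | 3.0% |
| 80 | 0.1% | 0.08 | 7.7% |
| 30 | 1.4% | 0.42 | 34% |
| 80 | 1.4% | 1.12 | 68% |

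Sensitivity would rest on roughly zero or one case across the whole study.

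**What PABAK gives a nurse who always says normal.** PABAK = 2 × observed agreement − 1. Such a nurse's expected agreement is 1 − p, so the expected PABAK is 1 − 2p:
- no cases: 1.00
- p = 0.1%: 2 × 0.999 − 1 = 0.998
- p = 1.4%: 2 × 0.986 − 1 = 0.972

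A near-perfect value therefore does not separate a skilled reader from one who never calls a hip abnormal.

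**Precision of a reading test after training.**
- Assumptions: 10 abnormal images, all read by 30 to 40 nurses; sensitivity 80%; within-image correlation 0.1. The article gives none of these.
- Design effect for m nurses per image = 1 + (m − 1) × 0.1, which is 3.9 for 30 nurses and 4.9 for 40.
- Half-width = 1.96 × √(0.8 × 0.2 × design effect / readings).
- 30 nurses, 300 readings: 1.96 × √(0.16 × 3.9 / 300) = 0.089.
- 40 nurses, 400 readings: 1.96 × √(0.16 × 4.9 / 400) = 0.087.

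The half-width is about 9 points before any allowance for clustering by nurse. More nurses barely help when all read the same images; more distinct images do. Only nurses who pass the OSCE reach this stage, so 30 to 40 is an upper bound.

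**The case against.** The strongest reply is that reading is measured at the end of training. Agreement with the physician is evaluated in the unsupervised examination, and sensitivity and specificity of the nurse's ultrasound are planned. This stands. A reader might infer that the e-learning test is the only test of telling normal from abnormal; the article does not support that. The point is narrower: it is the only step that clearly includes abnormal images.

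A second reply is that no criterion in section 2.3 requires normal hips, so an abnormal hip could turn up. That is possible, and the calculation allows for it. At the article's own rates it yields too few cases to estimate sensitivity.

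A third is that obtaining the plane is a reasonable primary outcome for a training study of this size, that the Abstract defines it openly, and that the article nowhere says detection skill will be concluded from the primary outcome alone. All of this stands. The point does not require another primary outcome and predicts no misreporting.

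A reader might also infer that the image items are diluted by questions on anatomy or ultrasound basics. The article does not support this: tests are set per module, image reading is named in a module title, and nothing says the scores are pooled.

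**Conclusion.** The point holds in this form: the primary outcome is relevant to the aim but not sufficient for it, and the secondary reading measures cannot fill the gap with the subjects described. Sensitivity is undefined if all the infants have normal hips. Otherwise it rests on about 0.03 to 1.12 expected cases, assuming 30 to 80 infants and rates of 0.1% to 1.4%. A nurse who always says normal would have an expected PABAK of 0.97 to 1.00. The conclusion depends on Table 1 describing the infants correctly, or on opportunistic recruits having DDH at about the rates the article quotes. It does not depend on how the knowledge tests are scored.

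This is a mismatch between the stated aim and the stated outcomes and subjects, so a separate analysis plan could not repair it by choosing another statistic.

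**What to change.** 1. Keep the primary outcome, and word the conclusion drawn from it as skill in obtaining the standard plane.
2. Directly after the unsupervised examination, repeat the normal/abnormal image items with unseen, shuffled stored images of both classes. Report sensitivity and specificity against the known image label as a key secondary outcome, with intervals that allow for clustering by nurse and by image. Give nurses different image sets, or use more images, since the number of distinct images limits precision.
3. Base any statement about detecting DDH on that test. Report the clinical-training agreement and accuracy results as specificity-type evidence only, with the number of abnormal hips seen.

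The cost is a short extra test per nurse, a second set of stored images with known labels, and a narrower primary claim. No extra infants, staff or procedures are needed. Together with the e-learning result, the repeat also gives a comparison of reading before and after the hands-on stages, which suits the pre-post design.

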### 2.5. Statistical Analysis

Knowledge test results, OSCE scores, success rates of standard plane imaging, and time required for imaging will be reported using descriptive statistics. Inter-rater reliability will be reported using the prevalence adjusted bias adjusted kappa for each participant. The sensitivity and specificity of manual examination nurse and ultrasound examination by a nurse will be compared, with the diagnostic results from a physician as the gold standard.

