## 3. Conclusions

The nursing educational program, which focuses on ultrasound hip screening, will help improve nurses’ assessment skills and knowledge of suspicious DDH cases in newborns and infants during home visits. The current findings will provide crucial evidence to support the nursing profession in conducting ultrasound hip screening and in promoting accurate assessments during community-based newborns and infants home visit. The educational program addresses the issue of missed and late detection of DDH cases in resource-limited communities. This study will demonstrate the feasibility of procedures and the effectiveness of the educational program in 2024. 

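### The primary success rate is only described, with no pre-training value, comparator or success criterion, so it cannot demonstrate that the programme is effective

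*Protocol article*

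**What the plan says.** Section 2.4.3 names the primary outcome: "The primary outcome of this study will be the success rate in the unsupervised examination". It is scored from 0 to 100%. Section 2.5 gives its whole analysis: "success rates of standard plane imaging, and time required for imaging will be reported using descriptive statistics".

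Section 2.1 labels the design: "we developed an educational program for nurses with a pre-post design". The Abstract uses the same label. Section 2.3 sets the order of events: e-learning, hands-on seminar, OSCE, then clinical training for those who pass. In the second half of clinical training, "participants will independently assess another infant without supervision".

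The number of nurses is set by resources (section 2.2): "We will recruit approximately 30–40 nurses to consider the feasibility and limited budget". The Conclusions, like the Abstract, state what will follow: "This study will demonstrate the feasibility of procedures and the effectiveness of the educational program in 2024".

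**The concern.** To say that a training programme is effective is to say that performance is better than it would have been without the programme, or that it reaches a level fixed beforehand as good enough. The plan supplies neither for its primary outcome. There is no untrained or differently trained group, no measurement before training, and no target rate.

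The rate also describes a selected group, because nurses who fail the OSCE never reach the measurement. A high rate could reflect the programme, the selection, or skill already present, and nothing in the plan separates these.

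At stake is the study's main conclusion. Followed exactly as written, the plan leads to an effectiveness statement that its primary outcome can neither support nor refute.

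**Working it through.** **1. Could the pre-post design supply the comparison?** Candidate baselines in the Protocol article:

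| Candidate | Where | Is it a baseline for the primary outcome? |
|---|---|---|
| Knowledge tests in the modules | 2.4.1 | No. A different measure, tied to the course content |
| OSCE on a phantom | 2.3, 2.4.2 | No. A different measure, taken after phantom training, and a gate to the next step |
| Supervised examination | 2.3, 2.4.3 | No. The same measure, but after the same e-learning and seminar, and with physician guidance |
| Manual against ultrasound examination | 2.5 | No. It compares the accuracy of two methods, not imaging success before and after training |

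None gives a pre-training value of imaging success.

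**2. Could the sample size imply a target?** The 30 to 40 nurses rest on feasibility and budget. No expected rate, benchmark, alpha, power or precision is stated, so there is no planning figure to reproduce and no target to infer.

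**3. Who is in the denominator?** Let s be the share of nurses passing the OSCE and q the success rate among them. The reported rate is q. If nurses who fail the OSCE counted as unsuccessful, the rate for all trained nurses would be s × q, which is lower whenever s is below 1. The document gives no value of s. The figures below take all 30 or 40 nurses as reaching the measurement, which is the favourable case.

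**4. How precise would the rate be?** Assumptions: one result per nurse, observed rate 80%. Exact (Clopper-Pearson) 95% limits for x successes in n are the 2.5% quantile of Beta(x, n − x + 1) and the 97.5% quantile of Beta(x + 1, n − x).

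- n = 30, x = 24: 61.4% to 92.3%
- n = 40, x = 32: 64.4% to 90.9%

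**5. What could a benchmark show?** Assumptions: one result per nurse, true rate 90%, one-sided alpha at most 0.025. The rule is the smallest k with P(X ≥ k | n, benchmark) ≤ 0.025. Power is P(X ≥ k | n, 0.90). The benchmarks are illustrations only.

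| Benchmark | n | k | Actual alpha | Power |
|---|---|---|---|---|
| 70% | 30 | 27 | 0.009 | 0.65 |
| 70% | 40 | 34 | 0.024 | 0.90 |
| 80% | 30 | 29 | 0.011 | 0.18 |
| 80% | 40 | 38 | 0.008 | 0.22 |

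What 30 to 40 nurses can show depends on a benchmark that has not been set.

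**6. Why take the nurse as the unit?** This is an illustration only, since the article does not fix the number of hips per nurse. Assume two hips per nurse, 30 nurses, a rate of 80% and a within-nurse intraclass correlation (ICC) of 0.5. The half-width is 1.96 × √(0.8 × 0.2 × DE / 60), with design effect DE = 1 + ICC.

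- DE = 1 (hips independent): 10.1 points
- DE = 1.5: 12.4 points

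Under these assumptions, treating hips as independent would make the half-width about 18% too small (1 − 1/√1.5).

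**The case against.** The best defence is that this is a small study sized on feasibility and budget, and that description suits such a study. The source is a journal article, so interval methods, unit of analysis and handling of clustering may stand in a fuller document that is not shown. A go/no-go threshold is partly a matter of preference.

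Much of this stands. Description is a legitimate plan, and the absence of an interval method from the article is not in itself a defect. What does not stand is the combination. The article states its primary analysis as description and also states an effectiveness conclusion. That conflict lies in the shown text, and a better interval would not resolve it.

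Three stronger readings are tempting and are not supported.

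- **That the plan's interval would be too narrow because hips are treated as independent.** The article proposes no interval and no pooling of hips. If each nurse contributes one percentage and these are summarised over nurses, within-nurse correlation is already absorbed.
- **That each nurse contributes exactly two hips from one infant, or that the five nurses in a session share an infant.** Section 2.3 speaks of another infant but fixes no number of hips, images or attempts. Table 1 allots 90 minutes to the unsupervised part. Its footnote on five participants explains only how the durations were counted.
- **That the investigators intend to call any result effective.** No decision rule of any kind is stated. The fault is that the rule is absent, not that a lax one is present.

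**Conclusion.** The point holds in this form: the primary outcome is a single post-training percentage in nurses who passed the OSCE, with no pre-training value, comparator or success criterion, and it cannot demonstrate effectiveness. This rests on the wording of sections 2.1, 2.3, 2.4.3, 2.5 and 3 and needs no assumption.

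The figures are illustrations. With one result per nurse and an observed 80%, the compatible true rates run from just above 60% to just above 90%. Against an assumed true rate of 90%, power runs from 0.18 to 0.90 across the benchmarks and sample sizes tried. The clustering figures depend further on an assumed ICC and number of hips per nurse, and they do not carry the point.

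Nothing here suggests that the programme does not work. The finding concerns what the stated analysis can show. It should be corrected before clinical training begins, and the correction is mainly one of wording.

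**What to change.** Choose one of two routes before the first clinical session.

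- **Limit the claim.** In the Abstract and Conclusions, replace the effectiveness statement by feasibility and descriptive post-training performance among nurses who reach clinical training. The cost is a less favourable claim.
- **Set a criterion.** State a minimum acceptable success rate, chosen and justified by the investigators, and judge the primary estimate against it, for example by requiring the lower 95% limit to exceed it. The cost is limited power with 30 to 40 nurses if the benchmark lies close to the true rate, as the table shows. Meeting a benchmark would show adequate performance after training, not improvement caused by it.

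On either route:

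- Report the primary rate with a 95% interval that takes the nurse as the unit, or the session if infants are shared between nurses.
- State what counts as one attempt.
- Report how many nurses enrolled, passed the OSCE and were measured.
- Drop the pre-post label for the primary outcome, or say which measure it refers to.

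The reporting changes need no further nurses or scans. A demanding benchmark might.
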